## Abstract

**Background:**

Bodily illusions can be used to investigate the experience of being in a body by manipulating the underlying processes of multisensory integration. Research suggests that people with eating disorders (EDs) may have impairments in visual, interoceptive, proprioceptive, and tactile bodily perception. Furthermore, people with EDs also show abnormalities in integrating multisensory visuo-tactile and visual-auditory signals related to the body, which may contribute to the development of body image disturbances. Visuo-auditory integration abnormalities have been observed also in people with subthreshold ED symptomatology. However, it remains unclear whether these impairments are specific to bodily signals or if they extend to any auditory signals.

**Methods:**

We will recruit 50 participants (aged 18–24; females assigned at birth) with ED symptomatology (subthreshold group) and 50 control participants. The Eating Disorder Examination Questionnaire will be administered to screen for ED symptomatology and divide the sample into two groups accordingly (control and subthreshold group using a clinical cut-off score of 2.8). The strength of both illusions will be measured implicitly with estimations of body part position and size, and explicitly with self-report questionnaires. As a secondary aim, regression analysis will be run to test the predictive role of susceptibility for both illusions on interoceptive body awareness (measured by the Multidimensional Assessment of Interoceptive Awareness Scale) and sensory-processing sensitivity (measured by the Highly Sensitive Person Scale).

**Discussion:**

Our study may contribute to our understanding of the mechanisms underlying body image disturbances. The results may pave the way for novel clinical interventions targeting early symptoms prior to the development of the disorder in young females.

**Supplementary Information:**

The online version contains supplementary material available at 10.1186/s40337-023-00749-4.

## Background

Body image disturbance (BID) is a clinical feature commonly associated with eating disorders (EDs) [1, 2]. BID is a multidimensional construct comprising two components: an attitudinal component (i.e., negative feelings and thoughts toward the body) and a perceptual component (i.e., inability to accurately estimate body size) [2]. Traditionally, the former has played a crucial role in cognitive-behavioral therapies whereas the latter has been largely overlooked [2, 3], and thus its relevance to clinical practice remains unclear [4]. Experimental evidence suggests that people with Anorexia Nervosa (AN) and Bulimia Nervosa overestimate the body size compared to control participants [4, 5]. Furthermore, the perceptual component of BID in people with AN has been linked to poorer therapeutic outcomes, namely increased cognitive, affective, and behavioral psychopathology [6, 7]. Importantly, neurobiological studies using functional magnetic resonance imaging (fMRI) have associated impairments in the perceptual component in people with AN with structural–functional brain abnormalities in areas involved in the processing of body-related information (e.g., alterations of the precuneus or parietal cortex, among others) [7, 8]. Taken together, this body of literature suggests that the perceptual component of BID is a crucial clinical feature in EDs that requires more attention and must be targeted using specialized treatments [4, 6].

The perceptual component of BID might be a contributing factor in the onset, maintenance, and relapse of EDs, although evidence in this direction is still sparse [3]. However, recent developments in the field of multisensory integration can fill this gap by uncovering the processes underlying the perception of one’s own body, and by implications shed some light on the aetiological basis underlying perceptual disturbances in body image [9]. Ongoing research in this field suggests that our body image is not static, but it is continuously updated responding to the inputs that we receive from our body (i.e., visual, auditory, or haptic signals, among others) [9, 10]. This idea is supported by studies using multisensory body illusions, which have shown the malleability of body image, and overall mental body-representations, in response to conflicting sensory inputs [10, 11]. In broad terms, these body illusions could be defined as any “psychological phenomenon in which the perception of one's own body importantly deviates from the configuration of the physical one, e.g., in terms of size, location, or ownership” [12]. For example, as a prototypical paradigm, the Rubber Hand Illusion showed that it is possible to induce participants to perceive a rubber hand as part of their body by touching a fake hand in synchrony with the participant’s own hand, which is out of view (visual–haptic–proprioceptive integration) [11]. Inspired by this promising line of research, studies applying body illusions to investigate the perceptual component of BID on clinical conditions, including EDs, are on the rise [13].

Mussap and Salton [14] used the rubber hand illusion to evaluate the relationship between body image perception and ED symptomatology. Their results suggest that participants with ED symptomatology were significantly more susceptible to the illusion as compared to people without ED symptomatology. Thus, they concluded that body image malleability could be a risk factor for developing EDs given the significant relationship between the susceptibility to the illusion with ED symptomatology, such as bingeing and purging behaviors. Along the same line, subsequent studies corroborated and extended these findings in EDs samples. For example, Eshkevari et al. [15] found that participants with EDs experienced the illusion when the rubber hand and the participant’s own hand were touched asynchronously (i.e., a condition that does not lead to the illusion in healthy individuals) [15, 16]. In another study, Keizer et al. [17] used the ‘Full Body Illusion’ to induce people with AN to feel as if a full-body avatar was their own body. They reported that after removing visual feedback of the participant’s own body, it was possible to reduce the overestimation of participants’ own body, with results lasting at least 2 h and 45 min after the illusion was induced. Overall, these findings show an increased sensitivity to visual information about the body and a decrease attention to body somatosensory and proprioceptive information processing [15–17]. However, studies in the field reveals that perceptual impairments relevant to BID may also be non-visual, including other modalities such as haptic perception, interoception, or proprioception, among others [18, 19]. Accordingly, it is crucial to elucidate what aspect of perceptual processing of bodily information, including multisensory integration, is altered in EDs [19, 20].

Importantly, despite the growing body of literature pointing to the importance of auditory cues on body perception in healthy individuals and various clinical populations [21], there is a lack of investigation about auditory-driven body perception in EDs [22]. Along this line, Tajadura-Jiménez et al. [23] found that people's perceptions of their own body weight can change depending on the frequency spectra of their footsteps sounds (see work on the so-called ‘Footsteps Illusion’; [23]). Among the main findings, participants reported their bodies as being thinner when hearing the higher frequencies of their footsteps sound (vs. a low frequency condition) [23]. Critically, in the ED field, to the best of our knowledge, only two studies have investigated the multisensory integration of auditory signals with other sensory signals. In the first study, Chirico et al. [22] used the ‘Sound-induced Flash Illusion’, in which a single flash is presented together with several auditory beeps, to show that temporal discrimination processing of visuo-auditory stimuli was impaired in patients with AN, as compared to healthy controls. In the second study, considering the above-mentioned literature indicating a stronger influence of external sensory signals on processing bodily information, Tajadura-Jiménez et al. [24] hypothesised that participants with high-ED symptomatology and participants with AN would experience an enhanced ‘footstep illusion’ compared with those with low-ED symptomatology and control participants. This is in line with the previous hypothesis suggesting an overreliance of exteroception in people with EDs [15–17]. Contrary to expectations, they found that the AN group and the high-EDs risk group reported their body as wider/heavier in the ‘High-Frequency’ condition compared to the ‘Control-condition’. Tajadura-Jiménez et al. [24] suggested that these abnormalities in multisensory integration of proprioceptive and auditory signals may explain the difficulties in updating bodily information in light of novel and sometimes surprising sensory signals, which might potentially contribute to the development of BID in EDs. However, it still remains unclear whether these impairments are specific to natural auditory signals related to body weight, which is an emotionallysalient aspect in people with EDs, or whether they correspond to a general impairment related to the monitoring and integration of any auditory signals in relation to one’s own body [24].

Given the lack of research, the primary aim of this study is to elucidate the link between body perception and non-naturalistic auditory information in participants with subthreshold ED symptomatology, as compared to participants without ED symptomatology, using two body illusions. Our primary objective is to investigate the effect of artificial non-naturalistic sounds on the perceived size of a finger in healthy individuals. Previous research has found that this type of sound, which does not contain information on body size, can elicit changes in the perceived size of a finger in a phenomenon known as the 'auditory Pinocchio' illusion [25]. In the first study to report this illusion, it was found that when healthy participants pulled the tip of their right index finger with their left hand and an ascending pitch sound was presented concurrently, the participants both felt and judged their finger to be longer than when the pull was combined with a descending pitch or a constant pitch sound [25]. This illusion builds on the well-known association between changes in pitch and changes in height or size (for a review see [26]). This illusion focuses on a body part (finger) that is not emotionally salient, reducing therefore ‘contamination' by cognitive processes [27]. Nevertheless, given the clinical relevance of studying emotionally salient body parts as they play an essential role in BID [4], and in order to extend the aforementioned research [24], we will adapt the 'auditory Pinocchio’ illusion to a body part that is particularly salient from the emotional point of view for the majority of EDs, namely the waist. We expect that the illusion also occurs for the waist (horizontal position) as for the finger (vertical position) since besides the correspondence with height, pitch is also associated to physical size (at least in the visual domain): static high and low pitches are respectively associated to smaller and larger visual size [28], and ascending and descending pitches are respectively associated to growing and shrinking size [29]. This body of research holds the potential to provide experimental evidence supporting the development of novel therapies, which can target specifically the aforementioned distortions in the perception of sensory body signals, and ultimately BID (e.g., [30]).

For example, Mussap and Salton [14] noted, one explanation for individual differences in response to cognitive-behavior therapies may reflect differences in pre-existing levels of body-image flexibility (i.e., ability to openly perceive thoughts or sensations concerning the body without acting on or changing them) [14]. This line of reasoning is in accordance with a recent meta-analysis (N = 62) which indicated that higher body-image flexibility is associated with lower levels of body-image problems and ED symptomatology [31]. Thus, body-image flexibility may arise as a key psychological construct that may be enhanced during psychological interventions [31]. As such, both body illusions (affecting finger and waist mental representations) could be useful to potentially identify participants who will be most responsive to behavioural therapies, as those with heightened body-image flexibility. Given the lack of research, there is a need to test the association between body-image flexibility and key psychological constructs related to ED symptomatology in this area [31].

## Aim and hypothesis

### Primary exploratory aim: auditory-driven changes in body perception

The primary aim of this study is to gain an exploratory understanding of the influence on body perception of non-naturalistic auditory information in participants with subthreshold EDs symptomatology using two body illusions. The scarce literature on the topic precludes us from considering a confirmatory model. As a result, the following hypotheses are all descriptive–exploratory.

**Hypotheses 1 (H1)**: Participants with subthreshold ED symptomatology will differ from participants without ED symptomatology in their degree of body image distortion. This hypothesis is exploratory, as alternatively, both groups may show the same degree of distortion.

H1 is based on previous literature that has shown a conflicting set of results. While there is strong evidence to suggest that young females with ED symptomatology and individuals with EDs tend to overestimate their body size compared to control individuals, some evidence suggests that body image distortions are not specific to this population, implying that they can underestimate their body size [24] or even be as accurate as individuals without ED symptomatology [32].

**Hypotheses 2 (H2)**: Participants with subthreshold ED symptomatology will show stronger auditory-driven body illusions, compared to control individuals.

H2 is based on the traditional hypothesis in support of a stronger influence of external sensory signals, leading to stronger body illusions in people with and subthreshold EDs [15–17].

**Hypotheses 3 (H3)**: Participants with subthreshold ED symptomatology, as compared to without ED symptomatology, will present unusual patterns of results in the finger elongation or shrinking waist illusion, suggesting impairments in the integration of artificial auditory signals into their body image.

H3 hypothesizes that participants with subthreshold ED symptomatology, as compared to people without ED symptomatology, will present unusual patterns of results, that is, the perceived finger elongation or shrinking waist will not necessarily occur in the ascending pitch condition (or not only in that condition, as in [24]. The results will shed light on whether the alteration in the mechanisms integrating auditory signals into body image is present only to natural signals related to body weight/size (e.g., footsteps) or it is linked to any auditory signals.

**Hypotheses 4 (H4)**: Participants with subthreshold ED symptomatology, as compared to people without ED symptomatology, will experience the finger illusion but not the waist illusion, suggesting that the experience of the illusion is linked to the emotional salience of the body part rather than the nature of the auditory signals.

H4 hypothesizes that participants with subthreshold EDs symptomatology will experience the illusion for the finger (not emotionally salient body part), replicating previous research (see [25]) but not for the waist (emotionally salient body part). In that case, the experience of the illusion will not be linked to the nature of the auditory signals (natural sound vs. artificial sound), but to the emotional salience of the body part (finger vs. waist).

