Body visualizer task [44]	To assess the ability to accurately estimate body size (body size discrepancy) as well as the effects of sound feedback on perceived body size. Participants will adjust the weight related dimension of the body of a 3D avatar displayed on the screen to correspond to their perceived body size. Accuracy will be calculated according to the formula (estimated/actual body size) × 100 also-called body perception index (BPI) [45]. Specifically, a negative value represents an underestimation, whereas a positive value represents an overestimation	X		X

Body weight will be measured to the nearest 0.1 kg/% by means of a calibrated digital body fat scale (Sinocare CW 286). The Body feelings questionnaire will be directly built into Google Form and completed on a 10.1″ Android tablet (Lenovo M10)

^†^Spanish Version of the Eating Disorder Examination Questionnaire [46]

^‡^Spanish version of the Highly Sensitive Person Scale [47]

^§^The Multidimensional Assessment of Interoceptive Awareness [48]

Inclusion criteria will be: (a) normal (or corrected) auditory acuity; (b) sex: females (sex assigned at birth); (c) females within the healthy range of BMI (between 18.5 and 24.9) in order to reduce the likelihood of medical comorbidities that could affect the results (according to the World Health Organization index (WHO) [49]). Nevertheless, we recognize that weight/body mass index is not the sole predictor of potential co-occurring medical conditions. By doing so, we also avoid a potential confounding variable reported by [24]. This is in line with the criteria of healthy participants usually used in the field of eating disorders and body illusions research (e.g., [16]). Exclusion criteria: (a) lifetime history or presence of any significant brain injury, neurological condition, auditory pathology; (b) lifetime history or presence of a mental illness measured by self-report measures and screening questions; (c) lifetime history of underweight or overweight; (d) current use of psychotropic drugs (e.g. antidepressants) or intake of recreational synthetic or natural drugs; (e) inability to understand Spanish; (f) inability to provide consent; (g) out of age range; (h) pregnant status.

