#### Experiment 2 Procedure: Waist

First, to assess the degree of baseline body size discrepancy participants will complete the Body Visualizer task. The initial ‘weight’ of the avatar will be set to match the participant’s ± 25%. Participants will be instructed to adjust the avatar's body's 'weight' dimension. Whether the initial weight was + 25% or − 25% will be counterbalanced over two repeats, one after the other, and which together allows calculating the degree of body size discrepancy for each condition, by averaging the two responses. Later, the experimenter will measure the width of the participant’s waist using a paediatric stadiometer. Specifically, the location of the waist will be “the minimum horizontal circumference around the body at waist height” in line with the ‘Standard Terminology Relating to Body Dimensions for Apparel Sizing’ [51].

Subsequently, participants will be first required to complete an "anchor" task. In this task, participants will be asked to press and pull out their waist twenty times, an action that will trigger the ‘anchoring’ tone on each occasion. After completing the anchor task, a practice task will be presented, one trial for each feedback condition.

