#### Body visualizer task

The degree of body size discrepancy will be hand-coded by the experimenter into a data sheet. Per participant, a total of four summary estimations will be calculated [(baseline body size discrepancy) + (post-experiment body size discrepancy × 3 feedback conditions: ‘ascendent’, ‘constant’, ‘descendent’)] according to the BPI index (see Table 1 for more details).

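### H1 speaks of the degree of body image distortion, but the only planned score measures its average direction; an absolute discrepancy should be reported beside it

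*Protocol article*

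**What the plan says.** The protocol article, under the primary exploratory aim, gives H1 as "Participants with subthreshold ED symptomatology will differ from participants without ED symptomatology in their degree of body image distortion". The alternative it sets against this is "This hypothesis is exploratory, as alternatively, both groups may show the same degree of distortion". The rationale describes conflicting literature. It says there is strong evidence of overestimation relative to controls, and sets against it other evidence "implying that they can underestimate their body size [24] or even be as accurate as individuals without ED symptomatology".

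The measure is the Body Visualizer task in Table 1: "Accuracy will be calculated according to the formula (estimated/actual body size) × 100". The sign convention beside it is that "a negative value represents an underestimation, whereas a positive value represents an overestimation". The Experiment 2 procedure has two baseline adjustments, starting from +25% and −25%, "which together allows calculating the degree of body size discrepancy for each condition, by averaging the two responses". Under data management for this task, "Per participant, a total of four summary estimations will be calculated": one at baseline and one after the experiment for each of the three feedback conditions, all as BPI.

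Under Statistical analyses, the baseline score is compared between groups by a t-test or Wilcoxon test, and the later scores by a repeated-measures ANOVA. No absolute discrepancy is derived and no comparison of spread is planned. Finger and waist estimates are also compared between groups, but as estimates, not relative to the measured size.

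**The concern.** H1 and the label in Table 1 concern how far a woman's estimate lies from her actual size. The planned comparison concerns where the average estimate lies, above or below actual size. These are different quantities, and they can disagree in two ways.

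- **No difference found.** If one group contains larger errors in both directions, its mean signed error can equal that of the other group. A null result then does not support the stated alternative that the two groups are equally distorted.
- **Difference found.** If one group leans to overestimation and the other to underestimation by the same amount, the signed test separates them although the degree of distortion is equal.

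At stake is the wording of the H1 conclusion. The study is meant to prepare a confirmatory one, so it matters which construct its result describes.

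**Working it through.** **Inputs from the article.** 50 participants per group and alpha 0.05 (Sample size considerations); signed BPI, with group comparison by t-test or Wilcoxon test. The article states no power or SD for H1, so there is no H1 figure to reproduce. Its general remark that power may fall short at an effect size of 0.4 is consistent: √(50/2) × 0.4 = 2.0, and Φ(2.0 − 1.96) = 0.52, below 0.80.

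**Assumptions.** Let X = BPI − 100, so that 0 is a perfect estimate. The subtraction is needed because the printed ratio × 100 cannot be negative, which does not fit the sign convention beside it. Cancellation is the same on either scale. X is taken as normal with mean m and SD s; the values are assumed. Tests are two-sided and treat the groups as independent.

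**Formulas.**
- E|X| = s√(2/π)·exp(−m²/2s²) + m[1 − 2Φ(−m/s)]
- Var|X| = m² + s² − (E|X|)²
- Power ≈ Φ(|difference|/SE − 1.96), with SE = √((v₁ + v₂)/50)

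**Numbers put in.**
- *Means 0, SD 5 vs 10.* Signed difference 0, so rejection stays at 5%. E|X| = 0.798 × 5 = 3.99 and 0.798 × 10 = 7.98. Var|X| = 0.363 × 25 = 9.1 and 0.363 × 100 = 36.3. SE = √(45.4/50) = 0.95. Power ≈ Φ(3.99/0.95 − 1.96), about 0.99.
- *Means 0, SD 10 vs 12.5.* Signed difference 0, rejection 5%. E|X| = 7.98 and 9.97. SE = √((36.3 + 56.8)/50) = 1.36. Power ≈ Φ(1.99/1.36 − 1.96), about 0.31.
- *Means +10 vs −10, SD 5.* E|X| = 0.54 + 9.55 = 10.09 in both groups. Degree is equal, but the signed means differ by 20.
- *Means +5 vs 0, SD 10.* Signed: SE = √(200/50) = 2, power ≈ Φ(5/2 − 1.96) = 0.71. Absolute: E|X| = 8.96 vs 7.98, SE = √((44.8 + 36.3)/50) = 1.27, power about 0.12.

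**Simulation** (20,000 trials per row, t-test):

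| Means | SDs | Mean absolute error | Signed test rejects | Absolute test rejects |
|---|---|---|---|---|
| 0, 0 | 5, 10 | 3.99, 7.98 | 4.9% | 99.3% |
| 0, 0 | 10, 15 | 7.98, 11.96 | 5.1% | 74.0% |
| 0, 0 | 10, 12.5 | 7.98, 9.98 | 5.3% | 30.0% |
| +10, −10 | 5, 5 | 10.09, 10.09 | 100% | 5.0% |
| +5, 0 | 10, 10 | 8.95, 7.98 | 69.6% | 11.6% |

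A rank-sum test on the signed score behaves like the t-test: in the three zero-mean rows it rejects in 5.1% to 5.4% of trials (4,000 trials each).

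**The case against.** The article uses the word *degree* as its own label for the signed score, in the averaging rule, the summary scores and the covariate rule. On that usage hypothesis and measure agree. The H1 rationale is also largely directional: the literature places such groups above, below or level with controls, and a two-sided signed comparison separates those outcomes. This stands, and it is why the signed score must be kept.

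A reader might infer that, because the article cites both over- and underestimation, cancellation within the subthreshold group is likely. The text does not support that. It reports conflict in the literature about where such groups lie. It does not say that over- and underestimators are mixed in one group, and a mean near zero would run against the overestimation it calls strongly supported. A reader might also infer that the signed test is the wrong test of H1 and should give way to an absolute one. The mean-shift row shows otherwise: in the scenario the article considers best supported, the absolute score is the weaker test.

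Other points count in part. Group SDs or interquartile ranges and histograms would show a large difference in spread, but no planned test uses them. The processed data will be shared, so an absolute score could be derived later, though then only after the fact. All hypotheses are declared exploratory and limited power is acknowledged, which lowers the stakes without changing what the score measures. A condensed article may leave details to a fuller plan, but here the hypothesis, formula, sign rule, averaging and test are all stated, and the mismatch lies between them.

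**Conclusion.** The point holds as a mismatch between the wording of H1 and its only planned score. The signed BPI answers whether the groups differ in average over- or underestimation. Alone, it does not show that they share, or differ in, degree of distortion or accuracy. That follows from the definitions and needs no assumed SD.

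Its practical size is unknown, because the article gives no BPI variability. The contrast of about 5% against 99% is a worst case, resting on zero means in both groups and a doubled SD. A modest difference in spread (10 vs 12.5) gives 5% against 30%, and under a pure mean shift the advantage reverses, 70% against 12%. In an exploratory study this is an inexpensive improvement to the plan; it does not invalidate the planned comparison.

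**What to change.** 1. Define the signed discrepancy as BPI − 100 after averaging the two baseline adjustments, and keep it as the test of over- or underestimation.
2. Add |BPI − 100| per participant, computed from the same averaged score, as a second H1 score stated before the data are analysed.
3. Limit any statement that the groups show the same or a different degree of distortion, or accuracy, to what the absolute score supports. A non-significant absolute comparison should not be reported as proof of equality.

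The cost is one derived variable and one more exploratory test, with no new data. There is also a drawback in interpretation. The absolute score mixes systematic bias with response noise, because each baseline score averages only two adjustments. A group that merely responds less consistently would appear more distorted, and the report should say so.
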